**Cost**			
	Cost of providing the eHub, intersectoral service use, and effectiveness of eHub	Prospective cohort survey (6 months): Costs of implementation and national scaling of the model will be estimated (using study protocols, budgets, and population of children). The costs associated with caregiver-reported intersectoral service use will be estimated. Cost-effectiveness estimated based on the number of families engaged and those with unmet needs being met.	
**Demographics**			
	Postcode, single or couple parent, country of birth, language spoken at home, education status, number of adversities	Prospective cohort survey (baseline): The population cohort—eHub metadata will provide demographic characteristics of caregivers who access the eHub, including postcode to link SEIFA and parents’ place of birth compared with caregiver data from ABS.	

^a^eHub: Child and Family eHub.

^b^SEIFA: Socio-Economic Index for Area.

^c^IRSD: Index of Relative Socio-Economic Disadvantage.

^d^ABS: Australian Bureau of Statistics.

**Table 4 table4:** Secondary evaluation outcomes and associated measures.

Secondary outcomes: impact		Measure
**Information and service access and use**		
	Service access and use: Did the eHub assist caregivers with finding and connecting with relevant services including those relevant to social determinants of health and adversity? If not, why?	Prospective cohort survey (baseline and 6 months): Using the general [27] and actual [28] help-seeking questionnaires: Intention to seek help Actual help-seeking
	Information access and use: Did caregivers find the information needed? If not, why? Did accessing information change the caregiver’s behavior?	Prospective cohort survey (6 months): Did you find the information you needed? If not, why?
**Caregiver mental health**		
	Caregiver distress: Is eHub exposure associated with improvements in caregiver levels of distress?	Prospective cohort survey (baseline and 6 months): Kessler Psychological Distress Scale (K10) [29]
	Caregiver stress: Is eHub exposure associated with reduced caregiver stress related to (1) access to services and (2) their child’s mental health?	Prospective cohort survey (baseline and 6 months): Study designed Likert scale of stress

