### Recruitment

#### Prospective Cohort of Caregivers

The study will recruit 270 caregivers of children aged 0-12 years from the 3 identified sites (Table 1). To ensure representation of caregivers experiencing a range of adversities, the eHub will be advertised widely in the community in each site through posters and flyers with QR codes at physical primary care, community health and nongovernment organization hub sites, local community groups, schools, parent groups, playgroups, and social media to recruit caregivers with children aged 0-12 years. Interested caregivers will follow the QR code link to REDCap (Research Electronic Data Capture; Vanderbilt University)—a secure, web-based data capture platform hosted by the research team, where they can watch an informational video about the study and provide informed consent to be involved. Caregivers will then complete a baseline survey for the evaluation, including whether they meet the inclusion criteria (listed below); this will be our prospective cohort sample of caregivers. If caregivers respond “no” and would prefer not to participate in the evaluation, they can continue to use the eHub. eHub data analytics will be collected on all users of the eHub, including those involved in the evaluation and those who are not. Those not involved in the evaluation will not require consent to participate, as all eHub data analytics collected will be unidentifiable. Demographic details of participants will be collected through pop-up surveys on the eHub site. Figure 2 outlines the caregiver journey through the evaluation. Recruitment for the evaluation commenced in February 2024 and continued for each caregiver involved for 6 months.

The caregiver inclusion criteria are as follows: parents or primary caregivers with at least 1 child aged 0-12 years, noting that only 1 primary caregiver per family unit can enroll in the evaluation study; live in eligible intervention sites (Marrickville and Fairfield in New South Wales or Wyndham Vale in Victoria); can speak sufficient English to participate in the study and complete the survey, noting that although each of the study sites are culturally diverse, many residents speak English; and provide informed consent.

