**Child mental health**		
	Child mental health needs met: Did the caregivers’ child have unmet mental health care needs? If yes, were they met by the eHub resources?	Prospective cohort survey (baseline and 6 months): Unmet child mental health need [30]
	Child mental health symptoms: Is eHub exposure associated with improvements in parent-reported child mental health symptoms?	Prospective cohort survey Child aged 2 months to 2 years—Survey (baseline and 6 months) of Well-Being of Young Children [31] Child aged 2-12 years—Strengths and Difficulties Questionnaire [32]

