#### Statistical Methods for All Quantitative Outcomes

We will describe the characteristics of the caregivers and children using the mean (SD) and median (IQR) for continuous data (based on data distribution) and proportions for categorical data, at each time of measurement. To evaluate changes in key outcomes over time (baseline and 6 months), we will analyze the prospective cohort survey data using logistic and linear regression models for binary and continuous outcomes, respectively, specified in Table 3. Binary outcomes will be reported as odds ratios (as change in proportions) with 95% CIs; continuous outcomes will be reported as mean differences (as change in means) with 95% CIs. We will conduct a generalized estimating equation approach to account for repeated measures (ie, baseline and 6 months) for each participant. We will undertake stratified analyses by service site to explore whether outcomes vary by site. In consideration of the change in participants’ characteristics between baseline and 6-month surveys due to loss to follow-up, we will control for family socioeconomic characteristics. Missing data will be handled using appropriate statistical techniques (such as multiple imputation for missing at random). We will describe the proportions of measures derived from data analytics from eHub users (specified in Table 3). We will conduct all analyses using STATA (version 16) or SAS (SAS Institute) statistical software packages.

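### Three secondary questions ask about association with eHub exposure, but the stated model estimates only change over time in one cohort

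*Protocol article*

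**What the plan says.** Table 4 (secondary outcomes) words three impact questions as associations with exposure:

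- caregiver distress (K10): "Is eHub exposure associated with improvements in caregiver levels of distress";
- caregiver stress (a study-designed Likert scale): "Is eHub exposure associated with reduced caregiver stress related to" service access and the child's mental health;
- child symptoms (one of two instruments, by age): "Is eHub exposure associated with improvements in parent-reported child mental health symptoms".

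For each, the only measures listed are the outcome scales, which for distress and stress are collected at baseline and 6 months.

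The section on statistical methods for all quantitative outcomes gives the analysis: "To evaluate changes in key outcomes over time (baseline and 6 months), we will analyze the prospective cohort survey data". The reported quantity is a change over time: "continuous outcomes will be reported as mean differences (as change in means) with 95% CIs". On correlation within caregivers it says "We will conduct a generalized estimating equation approach to account for repeated measures (ie, baseline and 6 months) for each participant", and on adjustment "we will control for family socioeconomic characteristics". Site enters through stratified analyses. The analytics from eHub users are to be described as proportions. The section cites Table 3 for its outcomes although the mental health outcomes stand in Table 4; I take the same models to apply to both.

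The recruitment section says that analytics cover all users, inside and outside the evaluation. It explains that non-participants need no consent "as all eHub data analytics collected will be unidentifiable". Baseline is taken at first access to the eHub.

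**The concern.** An association with exposure needs caregivers who differ in exposure, or a comparison group without it. The stated model has neither. A caregiver who completes baseline and never returns contributes to the estimate in the same way as one who uses every tier.

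A fall in K10, stress or child symptom scores would therefore be reported under a question about the eHub, although the same fall could arise with no eHub effect. The Discussion makes this more likely. It hypothesizes that implementing the eHub will reduce caregiver distress and child mental health concerns, and it expects critical evidence on effectiveness for priority populations. Its stated limitations are the short follow-up and the English-language criterion; the absence of a comparator is not among them.

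**Working it through.** **1. What the model estimates.** With t = 0 at baseline and t = 1 at 6 months, the stated linear model is

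E(Y) = b0 + b1·t + g·(socioeconomic covariates).

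Here b1 is the mean at 6 months minus the mean at baseline. It is the sum of any eHub effect, secular change, regression to the mean, child ageing and selective follow-up. One coefficient cannot be split into these parts. An exposure question needs a further term, E(Y) = b0 + b1·t + b2·exposure + b3·exposure·t + covariates, and b3 would address it. No such term is stated.

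**2. The plan's own powered contrast.** Inputs from the sample size section: 270 caregivers, 10% loss (270 × 0.9 = 243), 9% rising to 20%, 90% power. Two-sided alpha 0.05 is my assumption. Treating the two time points as independent samples of 243:

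power = Φ{[0.11·√243 − 1.96·√(2 × 0.145 × 0.855)] / √(0.09 × 0.91 + 0.20 × 0.80)} = Φ{(1.715 − 0.976)/0.492} = Φ(1.50) = 0.933.

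With a continuity correction it is 0.916. The stated 90% is thus about reproduced, and only by comparing 6 months with baseline. The powered contrast is also a before-after change.

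**3. The plan's own background change.** The same section supposes a 5% increase without the intervention. Read as 5 percentage points (an assumption), service access goes from 9% to 14% with no eHub effect. For a paired comparison of 243 caregivers with within-person correlation ρ:

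- discordant proportion D = 0.09 × 0.86 + 0.14 × 0.91 − 2ρ·√(0.09 × 0.91 × 0.14 × 0.86) = 0.2048 − 0.1986ρ;
- probability of significance = Φ{[0.05·√243 − 1.96·√D] / √(D − 0.05²)}.

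| ρ | D | Probability |
|---|---|---|
| 0 | 0.205 | 0.41 |
| 0.3 | 0.145 | 0.53 |
| 0.5 | 0.106 | 0.67 |

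This concerns service access, not the three mental health scales. It shows how a time contrast behaves under a drift that the plan itself supposes.

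**4. Continuous scales.** The article gives no drift or correlation for K10, stress or child symptoms, so both are assumed. For a drift δ in SD units and correlation r, SE = √(2(1 − r)/243) and the probability of significance is Φ(δ/SE − 1.96).

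- r = 0.5: SE = 0.0642.
- r = 0.7: SE = 0.0497.

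| Drift, no eHub effect | r = 0.5 | r = 0.7 |
|---|---|---|
| 0.1 SD | 0.34 | 0.52 |
| 0.2 SD | 0.88 | 0.98 |
| 0.3 SD | >0.99 | >0.99 |

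For 0.2 SD: Φ(3.12 − 1.96) = 0.88 and Φ(4.02 − 1.96) = 0.98. Child symptoms are split by age between two instruments, so each has fewer than 243 pairs and the probabilities there are lower.

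**5. What an exposure contrast could detect.** If 243 completers are split by use, the difference detectable with 80% power is (1.96 + 0.84)·√(1/n1 + 1/n0), in SDs of the analysed score.

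| Share exposed | Detectable difference |
|---|---|
| 50% | 0.36 SD |
| 30% | 0.39 SD |
| 10% | 0.60 SD |
| 5% | 0.82 SD |

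The article expects 5%-10% of users to need the personal navigator (tier 4).

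**The case against.** **Baseline is pre-exposure.** The survey is completed at first access, so in a single-arm cohort the before-after contrast could be called the exposure contrast, and counting non-returners would suit an implementation study. The timing is correct. But exposure and time are then completely confounded, and an answer about exposure rests on assuming no other change.

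**Details belong in the analysis plan.** A condensed article may leave model terms to a fuller document, and the 6-month survey does ask whether caregivers found or used information, strategies and services. That is fair for omitted detail. Here, however, the article states the contrast, the reported quantity and the adjustment, and these do not match the questions it states.

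**The analytics.** A reader might infer that usage can never be attached to a cohort member, because the analytics are called unidentifiable. The documents do not support that. The clause gives the reason why people outside the evaluation need no consent. For consented caregivers, linkage is undescribed, not expressly ruled out.

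**Enrolment at a peak of distress.** A reader might also infer that scores must fall because caregivers enrol when seeking help. The article does not establish this: recruitment is through posters, schools, playgroups and social media, and no inclusion criterion requires distress or concern. Regression to the mean is possible, but its size is unknown.

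**An exposure term is not a cure.** This stands. Caregivers move to higher tiers because they need more support, so a contrast by use is open to confounding by need.

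**Conclusion.** The mismatch holds. As stated, the analysis can say whether scores changed over 6 months among enrolled caregivers. It cannot say whether eHub exposure was associated with the change. This follows from the wording and needs no numerical assumption.

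The size is illustrative. A drift of 0.2 SD with no eHub effect would be significant with probability about 0.88 to 0.98, assuming 243 complete pairs, r between 0.5 and 0.7 and two-sided alpha 0.05. A drift of 0.1 SD gives 0.34 to 0.52.

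A reader might infer that the evaluation as a whole fails. It does not: implementation outcomes are primary, impact is described as preliminary, and a type 3 design only observes impact. The point is limited to three secondary questions and the conclusions drawn from them.

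**What to change.** 1. Reword the three Table 4 questions as: did scores change over 6 months among enrolled caregivers?
2. Bring the matching Discussion statements (the hypothesis of reduced distress and child concerns, and the expected evidence on effectiveness) into line, and list the absence of a comparator as a limitation.
3. Optionally, add a secondary GEE with an exposure-by-time term. Build exposure from the 6-month adoption and use items already planned in Table 3, adjust for baseline need, and label the result observational.

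Items 1 and 2 need only text changes. Item 3 needs extra analysis but no new data. New survey items or tagged links are no longer practical, since data collection was scheduled to end in February 2025 and analysis was conducted from February to May 2025. Dissemination is planned for 2026, so the wording can still be settled before then.

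The price is a weaker stated claim. The optional contrast would remain open to confounding by need and would be imprecise for rarely used tiers.

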**Child mental health**		
	Child mental health needs met: Did the caregivers’ child have unmet mental health care needs? If yes, were they met by the eHub resources?	Prospective cohort survey (baseline and 6 months): Unmet child mental health need [30]
	Child mental health symptoms: Is eHub exposure associated with improvements in parent-reported child mental health symptoms?	Prospective cohort survey Child aged 2 months to 2 years—Survey (baseline and 6 months) of Well-Being of Young Children [31] Child aged 2-12 years—Strengths and Difficulties Questionnaire [32]

#### Continuous Learning and Improvement of the eHub Throughout Evaluation

Members from each evaluation site will form a project team alongside researchers to identify and respond to barriers for caregivers in accessing and engaging with the eHub. Using implementation science activities, the team will conduct 2-3 short Plan-Do-Study-Act quality improvement cycles [33] over the 6 months of implementation, including review of caregiver satisfaction with the navigation processes and content and whether caregivers are progressing to higher tiers of support. These short learning cycles will allow agile minor improvements of the eHub.

### eHub Outcome Data Collection (6 Months)

#### Prospective Cohort Caregiver Outcome Surveys (6 Months)

Caregivers involved in the evaluation will be sent an email or SMS text message invitation to complete an online survey at 6 months after baseline to measure outcomes on access and use of health services, accessibility, and overall experience of using the eHub. Secondary outcomes will also be measured via the caregiver outcome survey. All measures and associated data are outlined in Table 3. Surveys will be collected in REDCap, a secure online portal. Research assistants will follow-up those caregivers who do not complete the caregiver outcome survey via phone, text, or email.

#### Prospective Cohort Caregiver and Cross-Sectoral Service Provider Semistructured Interviews

Caregivers (n=15-20 in total) and intersectoral service providers (n=15-20 in total) from the evaluation sites will be invited to participate in individual semistructured interviews at 6 months after eHub implementation. Interviews will be conducted by web-conferencing platform (Zoom; Zoom Video Communications). Participants will be invited to provide their perspectives on barriers and enablers of using the eHub, such as were caregivers’ needs satisfied by using the eHub? Was the eHub able to support their unmet social needs? Did caregivers use or intend to use strategies provided in information sourced on the eHub? And were there changes to caregivers’ behavior (eg, help-seeking and implementing new strategies)? (see Multimedia Appendix 1 for interview guide). Participants will be invited to expand on any points they feel are important, and the interviewer may ask follow-up questions to elicit further details. The research assistant will be trained and experienced in qualitative methods; the interviews are expected to last between 20 and 30 minutes.

### Statistical Analysis

#### Sample Size Estimation for Impact Evaluation

We will recruit a total of 270 caregivers to give the study 90% power to detect an 11% increase in the proportion of caregivers accessing services via the eHub, that is, from 9% to 20% based on previous research [34], with a hypothetical 5% increase without the intervention. This allows for a 10% loss to follow-up.

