### Baseline Data Collection: Prospective Cohort Caregiver Baseline Survey

For those who consent to be involved in the eHub evaluation, when accessing the eHub for the first time, caregivers’ baseline data will be collected via an online survey, which includes the research measures outlined in Table 2. This online survey will be built into a secure online portal (REDCap) [25,26] through the eHub as outlined in Figure 3. If consented families do not complete the baseline questionnaire, they will be contacted by a research assistant by phone, email, or text to complete.

**Table 2 table2:** Study activities and timeline.

Activity	Timeline
Funding and concept development	December 2021
User-centered design and minimum viable product development	June 2022 to December 2023
Ethics approval	June 2023
Participant recruitment commenced	February 2024
6-Month evaluation period per participant	February 2024 to November 2024
Quantitative and qualitative data collection	February 2024 to February 2025
Data analysis	February 2025 to May 2025
Dissemination of findings	2026

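### The sample size is powered on access to services via the eHub rising from 9%, but that quantity is about 0% at baseline; the figures fit only access by any route, so the powered outcome is mislabelled

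*Protocol article*

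**What the plan says.** All statements are in the protocol article.

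- **Sample Size Estimation for Impact Evaluation.** A total of 270 caregivers is planned, for "90% power to detect an 11% increase in the proportion of caregivers accessing services via the eHub", the rise being "from 9% to 20% based on previous research [34], with a hypothetical 5% increase without the intervention". On attrition: "This allows for a 10% loss to follow-up".
- **Baseline Data Collection.** For consenting caregivers, "when accessing the eHub for the first time, caregivers’ baseline data will be collected via an online survey". Those who do not complete it are followed up: "If consented families do not complete the baseline questionnaire, they will be contacted by a research assistant by phone, email, or text to complete".
- **Table 4 (secondary outcomes).** The service question reads "Service access and use: Did the eHub assist caregivers with finding and connecting with relevant services". The measure, at baseline and 6 months, is "Using the general [27] and actual [28] help-seeking questionnaires: Intention to seek help Actual help-seeking".
- **Table 3 (primary outcomes).** The adoption item, which asks whether caregivers could find a suitable service or information, is collected at 6 months only.
- **Statistical Methods for All Quantitative Outcomes.** Baseline and 6 months are compared by logistic regression for binary outcomes, with generalized estimating equations for the repeated measures.

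**The concern.** A caregiver opening the eHub for the first time has not yet reached any service through it. If the baseline survey is taken then, the proportion reaching services via the eHub starts at about zero, and 9% cannot be its starting value. The second input fails in the same way: a rise in access via the eHub cannot occur without the eHub. Two of the stated planning values are therefore incompatible with the outcome they are attached to.

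This is the only sample-size basis in the article. If the label stays, a 6-month proportion could be reported as a powered increase in access via the eHub, although any use at all would count as an increase from a start near zero. Alternatively, the choice between any-route access and eHub access could be left open until the data are known.

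**Working it through.** **1. Inputs.** 270 caregivers in one cohort, 10% loss, 9% and 20% (sample-size section). Evaluable: 270 × 0.90 = 243. The section states neither the significance level nor the number of sides; two-sided 0.05 is assumed (z = 1.96).

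**2. The plan's own figure.** Treat 243 caregivers at each time as independent, with p₁ = 0.09, p₂ = 0.20, mean 0.145:

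- Standard error under no change: √(2 × 0.145 × 0.855 / 243) = 0.0319.
- Standard error under the alternative: √((0.09 × 0.91 + 0.20 × 0.80) / 243) = 0.0316.
- Power = Φ((0.11 − 1.96 × 0.0319) / 0.0316) = 93.3%. Subtracting a continuity correction of 1/243 from 0.11 gives 91.5%.

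The stated 90% is reproduced, slightly generously, as a before-after comparison of 9% with 20%. That comparison needs a real, non-zero baseline rate.

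**3. Which outcome can supply that rate?**

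| | Access via the eHub | Access by any route |
|---|---|---|
| Value at first eHub use | About 0%, apart from late baseline completers | Can be 9% |
| Rise without the intervention | Not possible | Possible |
| Listed at baseline and 6 months | No; the closest item (adoption, Table 3) is 6 months only | Yes; actual help-seeking (Table 4) |
| Pre-post model given | Not applicable | Yes; logistic regression with estimating equations |

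Only the right-hand column agrees with the planning values.

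**4. Power for the any-route outcome.** The baseline rate in this cohort is not known. The Early Intervention section of the Introduction gives 9%–27% for use of Medicare-rebated services by young children with emotional and externalizing problems. It cites a different reference from the sample-size section and describes a different population, so it serves here only to set an assumed range.

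For 243 pairs, baseline a, 6-month rate b = a + 0.11 and within-person correlation ρ:

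- p₁₁ = ab + ρ√(a(1−a)b(1−b)); discordant proportion q = a + b − 2p₁₁; d = 0.11.
- Power = Φ((d√243 − 1.96√q) / √(q − d²)).

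Example, a = 0.27, b = 0.38, ρ = 0: p₁₁ = 0.1026, q = 0.4448. Numerator 0.11 × 15.588 − 1.96 × 0.6669 = 0.408; denominator √(0.4448 − 0.0121) = 0.658. The ratio is 0.62, so power is 73%.

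| Assumed baseline → 6 months | ρ = 0 | ρ = 0.3 | ρ = 0.5 |
|---|---|---|---|
| 9% → 20% | 93% | 98% | 99.7% |
| 20% → 31% | 79% | 91% | 97% |
| 27% → 38% | 73% | 87% | 95% |

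These are powers against no change. They do not set the 6-month rate against the hypothetical background rise, which is a separate question.

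**5. Access via the eHub as a 6-month proportion.** At 20% with 243 caregivers, the 95% half-width is 1.96 × √(0.20 × 0.80 / 243) = 5.0 percentage points, so it can be described usefully without any baseline.

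**The case against.** The best defence is that the eHub phrase is loose wording. A background rise without the intervention makes sense only for any-route access, and 9% is a plausible any-route rate, so the intended outcome can be inferred. Table 4 measures service access and use at both times, the statistical methods section supplies a model, and the arithmetic reproduces. This largely stands, and it is why the point is one of labelling. It does not rescue the sentence: the article names one outcome and gives rates that belong to another.

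Two stronger readings are tempting, and the documents support neither.

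- *The sample size corresponds to no analysable outcome.* Actual help-seeking in Table 4 is collected twice and can be analysed by the stated model.
- *The planned analysis is decided in advance, or has no finite odds ratio because of an empty baseline cell.* That would need an item on access via the eHub asked at baseline, and none is listed.

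It is also fair to object that the lowest power, 73%, combines the top of a range from another population with zero correlation between two reports by the same caregiver, which is unlikely. At a correlation of 0.3 or 0.5, power at 27% is 87% or 95%. The direction in which this cohort departs from that range is unknown: having no need criterion points down, while including social services and recruiting at service sites point up. A loss of power is therefore possible but not shown.

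Finally, the exact binary cut and recall window may properly be left to a fuller document. The identity of the powered outcome is different, because the article states it and states it wrongly.

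**Conclusion.** The point holds as a mislabelled powered outcome. Access via the eHub is about 0% at baseline by the timing of the survey, cannot rise without the eHub, and is not listed for measurement at both times. The 9% to 20% figures fit only service access by any route.

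The numerical consequence is moderate. Under a two-sided 5% level, 243 pairs and an 11-point rise against no change, power ranges from 73% to 99.7% over assumed baselines of 9% to 27% and correlations of 0 to 0.5. In the tabulated cases it falls below 90% only at a 20% baseline with zero correlation, and at a 27% baseline with correlation 0 or 0.3.

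This should be fixed. It is not critical, because service access is a secondary outcome and the primary outcomes concern implementation.

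**What to change.** 1. In the sample-size section, remove the reference to the eHub route and name the Table 4 service access outcome as the powered pre-post outcome: actual help-seeking, by any route, with the same definition and recall window at baseline and 6 months.
2. Restate power with 243 pairs over a range of assumed baselines and within-person correlations, as tabulated above, and state the significance level and number of sides. Leave the sample size at 270. The Results section reports that the analysis ran from February to May 2025, so this is now a transparent correction.
3. Report access to a service via the eHub as a 6-month descriptive proportion with its confidence interval, not as a powered increase.

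The cost is a rewording of the sample-size section and of one row of Table 4. The instrument is already listed at both times, so no new data collection is needed. The drawback is that the restated power may look less favourable than 90%.

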Given the current gap in the existing “market” for this type of digital service, it will be essential to consider how best to learn from the evaluation to enhance its replicability to other sites. Furthermore, this study will provide insights into potential mechanisms underlying the intervention’s impact; shed light on the effectiveness, or ineffectiveness, of its various components; and offer possible explanations that will, again, be essential for replication.

Strengths of the study include its multisite design across 3 diverse communities, the use of real-world user data and embedded quality improvement processes, and the integration of caregiver and provider perspectives through semistructured interviews. One potential limitation of this study is the relatively short 6-month evaluation period, which may not capture long-term impacts on mental health outcomes or sustained service use. However, this time frame may be appropriate, given that digital applications are often designed for targeted, time-limited use, with peak engagement typically occurring during periods of greatest need or relevance to users. Another limitation is the inclusion criterion requiring sufficient English proficiency to participate in the study and complete the survey. Although each study site is culturally diverse and many residents speak English, this focus may limit the generalizability of findings to caregivers from non-English–speaking backgrounds.

Despite these limitations, this study will provide critical evidence on whether the eHub is effective in meeting the needs of priority populations and addresses inequitable access and uptake of support and services for families who are experiencing a range of adversities. Future directions may include testing longer-term outcomes of eHub use, examining cost-effectiveness over time, and adapting the platform for broader populations, including those speaking languages other than English. Results from this study may also inform the development of an implementation guide to support scale-up to other Australian sites.

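### The 90% power applies to the gross 9% to 20% change; the 5-point rise assumed without the eHub is never removed, and power for a rise beyond it is well below 90%

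*Protocol article*

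**What the plan says.** Sample Size Estimation for Impact Evaluation claims "90% power to detect an 11% increase in the proportion of caregivers accessing services via the eHub". It specifies the rise as "from 9% to 20% based on previous research [34], with a hypothetical 5% increase without the intervention", and adds: "This allows for a 10% loss to follow-up".

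The Abstract, Study Design and Recruitment sections describe a single prospective cohort from three sites. No comparison group appears anywhere.

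Statistical Methods for All Quantitative Outcomes models change between the two survey times: "We will conduct a generalized estimating equation approach to account for repeated measures (ie, baseline and 6 months) for each participant". Binary outcomes are reported as odds ratios with 95% CIs. The only covariates named are family socioeconomic characteristics, included because of loss to follow-up. No offset, margin or non-zero null is given.

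The Discussion hypothesises that implementing the eHub will produce more access to services, and says that "this study will provide critical evidence on whether the eHub is effective in meeting the needs of priority populations". Its limitations cover the short follow-up and the English-language criterion, but not the lack of a comparator.

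**The concern.** The sample-size sentence contains two effects. The gross change is 11 points. If 5 of those points would occur anyway, the part attributable to the eHub is 6 points. A before-after contrast in one cohort estimates the gross change, and its natural null is no change. Nothing in the analysis uses the 5 points.

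The stated power can therefore be taken as power to show what the eHub adds, which it is not. A significant time effect could also be read as eHub impact when the plan itself allows for a rise without the eHub.

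**Working it through.** **Inputs from the article.** 270 recruited, 10% loss, so 270 × 0.90 = 243 completers. Baseline 9%, 6 months 20%. Assumed rise without the eHub 5%, read as points (9% to 14%) because the same sentence calls 9% to 20% an 11% increase.

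**Assumptions.** The article does not state alpha, sidedness or within-person correlation ρ. I take two-sided 5%, in line with the 95% CIs, and ρ from 0 to 0.5. The largest ρ that margins of 9% and 20% allow is (0.09 − 0.018)/√(0.09 × 0.91 × 0.20 × 0.80) = 0.072/0.1145 = 0.63.

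**Step 1: reproduce the stated 90%.** Enter 20% and 9% as the two discordant proportions of a McNemar test: ψ = 0.29, d = 0.11.
- n = [(1.96√0.29 + 1.282√(0.29 − 0.0121))/0.11]² = 247.6, so 248. For 10% loss, 248/0.9 gives 276, or 248 × 1.1 gives 273.
- Power at 243 = Φ[(√243 × 0.11 − 1.96√0.29)/√0.2779] = Φ(1.25) = 89.4%.

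A two-proportion test of 9% against 20% at 243 per time point gives 93.3%, or 91.5% with continuity correction. With 9% and 20% as paired margins, power is 93.0% at ρ = 0, rising to 99.7% at ρ = 0.5. The stated 90% is met for the gross change. None of these calculations uses the 5%.

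**Step 2: power for a rise beyond 5 points.** Let p11 = p1p2 + ρ√(p1q1p2q2) and let v = p1 + p2 − 2p11 − (p2 − p1)² be the variance of the paired difference. Write v1 for 9% to 20% and v0 for 9% to 14%. The net effect is 0.20 − 0.14 = 0.06.
- Wald form (lower 95% limit above 5 points): Φ[0.06/√(v1/243) − 1.96]. At ρ = 0, v1 = 0.254 − 0.0121 = 0.2419 and SE = 0.0316, giving Φ(−0.06) = 48%.
- Null-variance form: Φ[(√243 × 0.06 − 1.96√v0)/√v1]. At ρ = 0, v0 = 0.2023, giving Φ(0.11) = 54%.

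**Step 3: drift alone.** If the truth is 9% to 14% and the test is against no change, power is Φ[(√243 × 0.05 − 1.96√ψ0)/√(ψ0 − 0.0025)], where ψ0 = 0.09 + 0.14 − 2p11. At ρ = 0, ψ0 = 0.2048 and the result is 41%.

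| ρ | Gross 9% to 20%, against no change | Beyond 5 points, Wald | Beyond 5 points, null variance | Drift only, significant against no change | Completers for 90% beyond 5 points (null variance; Wald) |
|---|---|---|---|---|---|
| 0 | 93.0% | 48% | 54% | 41% | 635; 707 |
| 0.3 | 98.2% | 61% | 68% | 53% | 451; 506 |
| 0.5 | 99.7% | 75% | 80% | 67% | 328; 372 |
| 0.63 | above 99.7% | 85% | 89% | 79% | 249; 286 |

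Completers needed are (1.96 + 1.282)²v1/0.06² for Wald and [(1.96√v0 + 1.282√v1)/0.06]² for null variance.

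**Sensitivity.**
- Odds-ratio scale, which is what the article reports: 20,000 simulated studies using a marginal logit with robust variance gave 41% to 70% significant under drift alone. Power against the drift odds ratio of (0.14/0.86)/(0.09/0.91) = 1.65 was 34% to 60%, for ρ from 0 to 0.5.
- One-sided 5%: net power is 60% to 84% (Wald) or 65% to 87% (null variance) for ρ from 0 to 0.5. It passes 90% only near the maximum ρ.
- If the 5% were relative (9% to 9.45%), net power would be about 92% or more and the power part of the point would fall. The sentence does not favour that reading.

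**The case against.** The strongest defence concerns scope. Implementation is the primary outcome; service access is secondary. The Abstract's objective speaks of preliminary impact, and a type 3 design observes impact while testing implementation. The mental health questions in Table 4 are framed as association. Other items ask caregivers directly whether the eHub helped, and interviews explore the same. The Discussion states a hypothesis rather than a decision rule, and its effectiveness sentence is not tied to the 9% to 20% test. All of this stands and lowers the severity. It does not reconcile the sample-size sentence with the analysis.

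Second, the article names no null. Testing against no change is an inference, though a before-after odds ratio with a 95% CI and no comparator has no other natural null. The article also calls the 5% hypothetical and does not say how it entered the calculation. A derivation may sit in a fuller document, but that could not supply the comparator that the described design lacks.

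Three stronger readings are tempting and should be resisted:
- A reader might infer that the 90% cannot be reproduced. It can, for the gross change (89.4% in Step 1).
- A reader might infer that a lower confidence limit above 5 points would establish an eHub effect. It would not: the 5 points are a hypothetical constant with no uncertainty attached, and the cohort remains uncontrolled.
- A reader might infer that the study must be enlarged or given a control arm. The Results section says that analysis ran from February to May 2025, and honest reporting needs neither.

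**Conclusion.** The point holds as a mismatch between what the power statement appears to cover and what the design can estimate. The 90% belongs to the gross 11-point change. Power for the net 6 points is about 48% to 80% for ρ from 0 to 0.5, and at most 85% to 89% at the maximum feasible ρ. The assumed drift alone would give a significant result in about 41% to 67% of studies for ρ from 0 to 0.5.

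These figures rest on 243 completers, a two-sided 5% level, the 5% read as points, and a null of no change. The exact values move with the variance form and the scale, so they should be given as ranges. Because the outcome is secondary and the repair is one of reporting, this should be fixed but does not undermine the study.

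**What to change.** Keep n=270 and change three places.

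1. Sample Size Estimation: say that the 90% power applies to the gross, uncontrolled change from 9% to 20%. Add that power for a rise beyond the assumed 5 points is well below 90%, giving the range with its alpha and correlation assumptions.
2. Statistical Methods: besides the odds ratio, report the change in proportion with its 95% CI next to the assumed 5-point drift. Label it uncontrolled change, describe it at most as exceeding the assumed drift, and do not credit it to the eHub.
3. Discussion: for service access, replace the effectiveness wording with association wording, and add the missing comparator to the limitations.

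The cost is text only, with no further participants or data. The stated power and the permitted conclusion become less favourable. Because the article reports the analysis as already conducted, a comparison with the 5-point drift that was added afterwards must be labelled post hoc.
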